# Protocol Synopsis

| **Study Title** | A Prospective, Open-label, Single-arm Phase II Clinical Study to Investigate the Efficacy and Safety of PD-1 Monoclonal Antibody in Combination with Thymalfasin and SOX Neoadjuvant Therapy in the Treatment of cStage III Gastric/Gastroesophageal Junction Adenocarcinoma |
| --- | --- |
| **Sponsor** | The First Affiliated Hospital of Nanjing Medical University (Jiangsu Province Hospital) |
| **Study Drugs** | Serplulimab, thymalfasin |
| **Study Phase** | Phase II |
| **Objectives** | To evaluate the efficacy and safety of Serplulimab in combination with thymalfasin and SOX regimen for neoadjuvant therapy of locally advanced gastric cancer |
| Endpoints | Primary endpoint:   - Pathologic complete response (pCR) rate;   Secondary endpoints:   - Clinical downstaging rate (T and/or N downstaging) after neoadjuvant therapy; - Tumor regression grade (TRG) after neoadjuvant therapy; - R0 resection rate after neoadjuvant therapy; - Major pathologic response (MPR) rate after neoadjuvant therapy; - Objective response rate (ORR) and disease control rate (DCR) after neoadjuvant therapy (RECIST v1.1); - Disease-free survival (DFS) and overall survival (OS) after neoadjuvant therapy; - Safety of neoadjuvant therapy (adverse reactions caused by drug treatment, perioperative complications, etc.).   Exploratory endpoint:   - Expression of CD68, CD86, CD163, CD4^+^ T cells, and CD8^+^ T cells in tumor tissue specimens. |
| **Study Design** | This is a prospective, single-center, single-arm, phase II clinical study. This study plans to enroll 30 treatment-naïve and operable patients with locally advanced adenocarcinoma gastric. After signing the informed consent form, patients will be screened to ensure they meet the inclusion and exclusion criteria. Before surgery, patients will receive three cycles of neoadjuvant therapy with Serplulimab combined with the SOX regimen and nine weeks of thymalfasin. The efficacy of neoadjuvant therapy and the feasibility of radical D2 resection will be assessed via imaging after Cycle 2 and Cycle 3. Radical gastrectomy will be performed within 2–6 weeks after completing the third dose. The postoperative treatment of patients will be jointly decided by clinical physicians and patients according to the actual conditions of clinical diagnosis and treatment.  The main observation indicator is the pCR rate after neoadjuvant therapy;  Safety assessment: The safety will be assessed once after each cycle of neoadjuvant therapy and at 30 days after surgery;  Event follow-up: The events will be followed up every 3 months during the first year after surgery, and once every 6 months from the first to the second years, until the second year. |
| **Inclusion Criteria** | Patients eligible for enrollment in this study must meet all of the following criteria:   1. Male or female patients aged 18–75 years with G/GEJ adenocarcinoma; 2. According to the AJCC 8th edition gastric cancer staging, patients with cStage III (cT_3-4a_N_1-3_M_0_) assessed by abdominal CT and G/GEJ adenocarcinoma diagnosed by gastroscopy and pathology (HER-2 negative or 1+); and patients with gastroesophageal junction (GEJ) cancer will only allow Siewert type III, and Siewert type II subjects who do not require combined thoracotomy to be enrolled. 3. Before enrollment, a doctor in charge of gastrointestinal surgery and an imaging technician jointly assess that the tumor is cStage III and qualified for the study of R0 resection with the purpose of cure, and the patient agrees to receive radical surgery and has no contraindication to surgery as judged by the surgeon; 4. No previous systemic therapy for the current disease, including surgical treatment, anti-tumor chemoradiotherapy/immunotherapy; 5. Expected survival of ≥3 months; 6. There are measurable tumor lesions according to RECISTv1.1 (see Attachment 3 for details); 7. ECOG PS score (see Attachment 4 for details) of 0–1 within 7 days after the first dose; 8. The heart is functioning well and resection for curative purposes can be performed. Patients with underlying ischaemic, valvular or other significant cardiac disease should be evaluated preoperatively by a cardiologist, if clinically indicated; 9. Primary organs are functioning normally and subjects are required to meet the following laboratory parameters:    1. Absolute neutrophil count (ANC) ≥ 1.5 × 10^9^/L in the absence of granulocyte colony-stimulating factor in the past 14 days;    2. Platelets ≥ 100 × 10^9^/L without transfusion in the past 14 days;    3. Hemoglobin > 9 g/dL without or erythropoietin use within the past 14 days;    4. Total bilirubin ≤ 1.5 × upper limit of normal (ULN); if total bilirubin > 1.5 × ULN but direct bilirubin ≤ ULN, the patient is also allowed to be enrolled;    5. Aspartate aminotransferase (AST) and alanine aminotransferase (ALT) ≤ 2.5 × ULN    6. Serum creatinine ≤ 1.5 × ULN and creatinine clearance (calculated using the Cockcroft-Gault formula) ≥ 60 ml/min;    7. Good coagulation, defined as international normalized ratio (INR) or prothrombin time (PT) ≤ 1.5 times ULN;    8. Normal thyroid function, defined as thyroid stimulating hormone (TSH) within the normal range. If baseline TSH is outside the normal range, subjects with total T3 (or FT3) and FT4 within the normal range can also be enrolled;    9. Myocardial enzymes within the normal range (subjects with isolated laboratory abnormalities judged as not clinically significant by the investigator are also allowed to be enrolled); 10. Thyroid function indicators: thyroid stimulating hormone (TSH) and free thyroxine (FT3/FT4) within the normal range or with mild and clinically insignificant abnormalities; 11. Body weight above 40 kg (including 40 kg), or BMI > 18.5; 12. Female patients must meet:  - Patients with menopausal (defined as no menses for at least 1 year and no other confirmed cause other than menopause) status, or who have been surgically sterilized (removal of ovaries and/or uterus), or who are of childbearing potential must also meet the following requirements: - Pregnancy test must be negative within 7 days prior to first dose; - Agree to use contraception with an annual failure rate of < 1% or remain abstinent (avoid heterosexual intercourse) from signing of informed consent through at least 120 days after the last dose of study drug and for at least 9 months after surgery (contraceptive methods with an annual failure rate of < 1% include bilateral tubal ligation, male sterilization, correct use of hormonal contraceptives that can inhibit ovulation, hormone-releasing intrauterine devices, and copper-containing intrauterine devices.) ; - Do not breastfeed.  1. Male patients must meet:   Agree to practice abstinence (avoid heterosexual intercourse) or use contraception as defined below: Male patients must remain abstinent or use condoms correctly for at least 120 days after the last dose of study drug and for at least 9 months after surgery if the partner is a woman of childbearing potential or if the partner is pregnant. Reliability of sexual abstinence should be evaluated with reference to the duration of the clinical study, patient preferences, and lifestyle of daily living. Periodic abstinence (eg, calendar day, ovulation, basal body temperature, or post-ovulation contraceptive methods) and withdrawal are not acceptable methods of contraception;   1. Subjects read and fully understood the patient information and signed the informed consent form. |
| **Exclusion Criteria** | Subjects who meet any of the following criteria will not be enrolled in this study:   1. Patients with prior (within 5 years) or concurrent other malignancy. Patients with cured localized tumors, such as cutaneous basal cell carcinoma, cutaneous squamous cell carcinoma, superficial bladder cancer, prostate carcinoma in situ, cervical carcinoma in situ, breast carcinoma in situ, stage I lung cancer, and stage I colorectal cancer, can be enrolled; 2. Patients who are scheduled to undergo or have previously undergone organ or bone marrow transplant; 3. Patients who have received blood transfusion within 2 weeks before the first dose or have a history of bleeding, and experience any bleeding event with a severity of grade 3 or higher based on CTCAE 4.0 within 4 weeks before screening; 4. Patients with abnormal coagulation function and bleeding tendency (INR > 1.5 in the absence of anticoagulants); patients treated with anticoagulants or vitamin K antagonists such as warfarin, heparin or their analogues; patients treated with low-dose warfarin (1 mg orally once daily) or low-dose aspirin (no more than 100 mg daily) for preventive purposes are allowed under the premise of prothrombin time international normalized ratio (INR) ≤ 1.5; 5. Have a history of arterial/venous thrombotic events within 6 months before screening, such as cerebrovascular accident (including transient ischemic attack), deep venous thrombosis (venous thrombosis caused by venous catheterization for previous chemotherapy is excluded if the investigator judges that the patient has recovered) and pulmonary embolism; 6. Have a history of myocardial infarction and poorly controlled arrhythmia within 6 months before the first dose (including QTc interval ≥ 450 ms for males and ≥ 470 ms for females) (QTc interval are calculated with Fridericia formula); 7. Presence of NYHA criteria class III-IV cardiac dysfunction or echocardiography: LVEF (left ventricular ejection fraction) < 50%; 8. Urine routine suggests urine protein ≥ + + and confirms 24-hour urine protein > 1.0 g; 9. There are multiple factors affecting oral medication (such as inability to swallow, chronic diarrhea and intestinal obstruction, etc.); 10. Pleural or peritoneal effusion with clinical symptoms requiring clinical intervention; 11. Human immunodeficiency virus (HIV) infection; 12. Active pulmonary tuberculosis; 13. Chronic unhealed wounds or incompletely healed fractures; 14. Patients with previous and current interstitial pneumonia, pneumoconiosis, radiation pneumonitis, drug-related pneumonia, severely impaired pulmonary function, etc. that may interfere with the detection and treatment of suspected drug-related pulmonary toxicity; 15. Presence of known active or suspected autoimmune disease, except for those who are in a stable state at enrollment (not requiring systemic immunosuppressive therapy); 16. History of severe chronic autoimmune diseases, such as systemic lupus erythematosus; history of inflammatory bowel diseases such as ulcerative enteritis and Crohn 's disease; history of chronic diarrheal diseases such as irritable bowel syndrome; history of sarcoidosis or tuberculosis; history of active hepatitis B and C and HIV-infected patients; patients with well-controlled non-serious immune diseases, such as dermatitis, arthritis, psoriasis, etc., can be enrolled. Patients with hepatitis B virus titer < 500 copies/ml can be enrolled; 17. Patients requiring treatment with systemic corticosteroids (at dose level > 10 mg/day prednisone efficacy) or other immunosuppressive drugs within 14 days prior to the first dose or during the study. However, enrollment is permitted if: In the absence of active autoimmune disease, patients are permitted to use topical or inhaled steroids, or adrenal hormone replacement therapy at dose level ≤ 10 mg/day prednisone efficacy; 18. Any active infection requiring systemic anti-infective treatment within 14 days before the first dose, with the exception of prophylactic antibiotic therapy (eg, prevention of urinary tract infection or chronic obstructive pulmonary disease); 19. Treatment with live vaccines within 28 days prior to the first dose; except for inactivated viral vaccines for seasonal influenza; 20. Prior treatment with antibody/drug therapy against immune checkpoints, such as PD-1, PD-L1, CTLA-4 inhibitors; 21. Treatment with related drugs or medical technology affecting immunity within 6 months prior to the first dose (including but not limited to: thymopentin, thymalfasin, interferon, CAR-T therapy, etc.); 22. Patients who are receiving other clinical study treatment, or planning to start this study treatment less than 1 month before the end of previous clinical study treatment; 23. Known history of allergy or intolerance to any study medications or their components; 24. Patients with a history of alcohol abuse, drug abuse and drug abuse. Patients who have stopped drinking alcohol can be enrolled; 25. Patients who do not follow the doctor 's advice, do not take medicine according to the regulations, or have incomplete data that may affect the efficacy judgment or safety judgment; 26. Pregnant or lactating female patients; 27. Patients with conditions that may increase the risk of study participation and study medications, or other severe, acute, or chronic diseases that, in the judgment of the investigator, will make them inappropriate for participation in a clinical study. 28. Patients with other conditions unsuitable for this clinical trial judged by the investigator. |
| Administration Method of the Study Drugs | Neoadjuvant therapy phase:  Serplulimab: 300 mg, i.v., D1, Q3W;  Thymalfasin: 4.8 mg, subcutaneous injection, twice a week. On Day 1 and Day 4 of each week during Weeks 1–9 or until surgery;  Oxaliplatin: 130 mg/m2, i.v., D1, Q3W;  Tegafur: oral administration: body surface area < 1.25 m^2^, 40 mg each time; body surface area ≥ 1.25 to < 1.5 m^2^, 50 mg each time; body surface area ≥ 1.5 m^2^, 60 mg each time, twice daily for each treatment cycle at D1-D14  After 3 courses of treatment before surgery, radical gastrectomy will be conducted based on evaluation by the investigator within 2–6 weeks after completion of chemotherapy + immunotherapy.  Adjuvant therapy phase: The postoperative treatment of patients will be jointly decided by clinical physicians and patients according to the actual conditions of clinical diagnosis and treatment. |
| **Evaluation Criteria** | Efficacy evaluation:  Evaluation per RECIST v1.1 criteria:   - Pathologic complete response (pCR) rate, defined as the proportion of subjects with no residual viable tumor cells under microscopic examination and negative lymph nodes among the total subjects; - Major pathologic response (MPR) rate, defined as the proportion of subjects with ≤10% viable tumor cells in the resected specimen among the total subjects; - Tumor regression grade (TRG) - Objective response rate (ORR), defined as the proportion of subjects achieving complete response (CR) and partial response (PR) among the total subjects; - Clinical downstaging rate: ypT0 ratio, ypN0 ratio, and preoperative imaging clinical stage will be counted, respectively, to compare with baseline imaging clinical stage downstaging ratio. - Disease-free survival (DFS), defined as the time from surgery to the first radiological disease recurrence or death (whichever occurs first); - Overall survival (OS), defined as the time from enrollment to death of the subject due to any cause;   Safety evaluation:   - Drug-related safety (per CTCAE 5.0): incidence, relationship to study drug and severity of TRAEs, TRAEs ≥ Grade 3, irAEs, etc. - Surgery-related safety (according to Dindo-Demartines-Clavien classification). |
| **Statistical Protocol** | General statistical analysis methods  All statistical analyses will be programmed and calculated using SPSS15 Statistical Analysis Software. Intergroup comparisons will be presented with 95% confidence intervals and p-values.  Unless otherwise specified, measurement data will be statistically described using mean ± standard deviation or median (minimum, maximum). Enumeration data will be statistically described using frequencies (percentages). |

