
1. **Background**

Gastric cancer (GC) is a primary malignant tumor of epithelial origin in the stomach. Among malignant tumors worldwide, gastric cancer has the third highest mortality rate, and in China, the incidence of gastric cancer ranks second only to lung cancer, and the mortality rate ranks third. In the world, there are about 1.2 million new cases of gastric cancer each year, and China accounts for about 40% of them. The proportion of early-stage gastric cancer in China is very low, only about 20%. Most cases are already in the advanced stage when they are detected, with a proportion as high as 50%–60%, and the overall 5-year survival rate is less than 50%. At present, radical surgery is still the only way to cure gastric cancer, but the surgical resection rate is low, and the R0 resection rate is about 70–80%; patients with stage II or higher have a high postoperative recurrence rate. Therefore, increasing the surgical resection rate and seeking other treatments that are more effective other than surgical treatment are the development direction of gastric cancer treatment research.

Neoadjuvant therapy can reduce tumor stage and increase the likelihood of complete tumor resection to achieve maximum pathological response. Today, the role of neoadjuvant therapy in potentially resectable gastric cancer is gradually being recognized. The results of a large multicenter MAGIC study from Europe showed that patients with potentially resectable gastric cancer who underwent surgery after neoadjuvant chemotherapy had a higher R0 resection rate (79.3% vs. 70.3%, P < 0.05), overall survival, progression-free survival, and 5-year survival rate (36% vs. 23%, P < 0.05) compared with patients who underwent surgery alone. The results of the FNCLCC/FFCD phase III clinical trial also showed that patients with resectable gastric cancer who underwent surgery after neoadjuvant chemotherapy were significantly better than those in the surgery alone group in terms of R0 resection rate (84% vs. 73%, P = 0.04), overall survival (P = 0.02), progression-free survival (P = 0.003), and 5-year survival rate (38% vs. 24%, P = 0.02). Both studies demonstrated the efficacy and safety of neoadjuvant chemotherapy for gastric cancer, and served as the key evidence for the inclusion of neoadjuvant chemotherapy in combination with surgical treatment in the NCCN guidelines for the diagnosis and treatment of gastric cancer.

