- Disease-free Survival (DFS): Disease-free survival refers to the time from the start of randomization to disease recurrence or death due to disease progression. DFS will be defined as the last date the patient is last confirmed to be disease-free survival if the patient does not experience disease progression during the study. Patients who discontinue the trial for reasons other than disease progression (no subsequent imaging) and patients who receive treatment after the trial will be censored at the time of discontinuation or the time of initiation treatment after the trial. When patients are not censored at the time of discontinuation from the trial or the time of initiation treatment after the trial, pre-planned sensitivity statistical analyses will further confirm DFS based only on the time of event of radiologically confirmed progression. New onset of other tumors are not considered as disease progression events and are not censored. If an imaging examination and evaluation show disease progression, the date of disease progression will not be the imaging examination date when disease progression is first shown, but the imaging examination date when disease progression is clearly confirmed. If disease progression is diagnosed by other clinical modalities, the date of diagnosis will be used as the date of disease progression.
- Overall Survival (OS): Overall survival refers to the date from enrollment to death due to any cause. For patients who are alive at last follow-up, their OS will be censored based on the time of last follow-up. For patients who are lost to follow-up, their OS will be censored based on the last confirmed survival time before loss to follow-up. The OS of data censor is defined as the time from enrollment to censoring.
- R0 resection rate: R0 resection rate refers to the proportion of patients who complete R0 resection in the total number of enrolled patients with surgically resectable gastric cancer through 3 cycles (21 days per cycle) of treatment with Serplulimab in combination with SOX regimen and 9 weeks of thymalfasin. Of these, R0 resection refers to negative microscopic margins.

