Imaging examinations will be performed to evaluate efficacy and feasibility of surgery after the completion of Cycles 2 and 3 of neoadjuvant therapy (within 7 days before the start of Cycle 3 and within 7 days after the end of Cycle 3). Imaging examinations are conducted after surgery and prior to adjuvant therapy, and pathological assessment will also be performed to evaluate the completeness of surgery. Evaluation requires a full abdominal direct contrast-enhanced (iodinated contrast) CT scan and gastric tumor MRI (contrast-enhanced). The same imaging technique should be used for pre- and post-evaluation in the same patient, and all imaging data must be retained. Patients who experience PD may continue the study treatment if they are willing and deemed suitable by the investigator to continue the original treatment regimen after re-signing the informed consent form, and re-evaluation will be performed after 4 weeks; otherwise, the patients will discontinue the study. For patients who discontinue treatment due to intolerable toxicity, if no efficacy evaluation is performed within 4 weeks prior to discontinuation, an efficacy evaluation should be conducted at the time of discontinuation.

For patients with potentially resectable gastric cancer after neoadjuvant therapy, surgery is scheduled within Weeks 2–6 after the completion of the last chemotherapy + immunotherapy. The surgical approach is determined based on the degree of disease response, including R0 resection, R1 resection, or cytoreductive surgery. The postoperative efficacy evaluation criteria primarily focus on surgical pathological assessment (complete pathological response rate, major pathological response rate, tumor regression grade, R0 resection rate, etc.), supplemented by imaging evaluation (objective response rate, disease control rate) for reference. At this point, the study has achieved its primary endpoint.

1. **Safety Reports and Adverse Event Management**
   1. **Definition of Adverse Event**

An adverse event (AE) is defined as any unfavorable and unintended medical occurrence in a clinical study participant from the time of signing the informed consent form, whether or not considered related to the study drug. AEs include, but are not limited to, the following circumstances:

- Exacerbation of pre-existing (prior to entering the clinical trial) medical conditions/diseases (including exacerbation of symptoms, signs, and abnormal laboratory findings);

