Per-protocol Set (PPS): Including all patients that comply with the study protocol, have good compliance, do not take prohibited medications during the study, and complete the required content in the case report forms. No imputation will be made for missing data. Statistical analyses of the drug's efficacy will be performed based on both the FAS and PPS.

Safety Analysis Set: Including all enrolled patients who have received at least one complete cycle of neoadjuvant immunotherapy plus chemotherapy and have safety records after using Serplulimab. This data set is used for safety analysis.

- 1. **Statistical Analysis Plan**

The results of this study will be primarily analyzed using statistical descriptive methods. For measurement data, the mean, standard deviation, median, max, and min values will be listed. For enumeration data and ranked data, the frequency (constituent ratio), rate, and CIs will be listed.

All statistical analyses will be programmed and calculated using SAS 9.2 Statistical Analysis Software. All statistical tests will be performed using two-sided tests, where P < 0.05 will be considered statistically significant for the tested differences, and CIs will be presented as 95% CIs.

- 1. **Efficacy Analysis**

The primary efficacy endpoint is the pCR rate. The ORR and its 95% CI will be calculated by the best overall response (BOR).

The Kaplan-Meier method will be used to plot the DFS curve and estimate the median DFS with its 95% CI, as well as the OS curve and its 95% CI.

Statistical analysis will be performed using SAS 9.4 software, where P < 0.05 will be considered statistically significant for the tested difference.

- 1. **Drug Safety Evaluation**

The AEs and adverse reactions that occurred in this study will be primarily described by descriptive statistical analysis, with a listing provided (adverse reactions are defined as “AEs with a ‘definitely related/probably related/possibly related’ relationship to the study drug”). The laboratory test results describe the conditions where values are normal before treatment but become abnormal afterward, along with the relationship with the study drug in case of abnormal changes. Chi-square test will be performed for the incidence of related adverse reactions between different stratified groups.

1. **Quality Control and Quality Assurance**

The study personnel must be physicians trained in clinical trials and work under the supervision of senior professionals.

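### Neither definition of disease-free survival requires the patient to be disease-free after surgery, although the protocol foresees R1 and cytoreductive operations

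*Protocol*

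**What the plan says.** The protocol defines DFS twice. The synopsis (Evaluation Criteria) has it "defined as the time from surgery to the first radiological disease recurrence or death (whichever occurs first". Section 2.2 says: "Disease-free survival refers to the time from the start of randomization to disease recurrence or death due to disease progression". Section 2.2 adds that a patient without progression is dated to the last time he or she was confirmed free of disease, and that starting treatment after the trial leads to censoring.

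Section 10 describes the operations expected after neoadjuvant therapy: "The surgical approach is determined based on the degree of disease response, including R0 resection, R1 resection, or cytoreductive surgery". Section 2.2 explains R0: "Of these, R0 resection refers to negative microscopic margins". An R1 or cytoreductive case is therefore not R0.

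On analysis, Section 12.3 states: "The Kaplan-Meier method will be used to plot the DFS curve and estimate the median DFS with its 95% CI". Section 12.1 adds: "Statistical analyses of the drug's efficacy will be performed based on both the FAS and PPS". The FAS is defined by receipt of serplulimab and one efficacy evaluation, the PPS by adherence. Neither is limited to patients with an R0 resection. On size, the synopsis says: "This study plans to enroll 30 treatment-naïve and operable patients".

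**The concern.** Disease-free survival has its plain meaning only for patients who are free of disease when the clock starts. The protocol names operations that leave tumour behind, yet neither definition excludes those patients or counts residual tumour at surgery as an event.

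Two quantities then share one curve: time to recurrence after a complete resection, and time to growth of tumour already known to be there. A reader of the median DFS could not tell how much comes from each. Patients in whom the regimen and surgery together did not clear the disease would contribute event-free time. With about 30 patients, a handful of such cases can move the curve.

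**Working it through.** The protocol gives no DFS target, event count or power figure, so there is nothing to reproduce. The check has two parts.

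**1. Applying the two definitions to three hypothetical patients**

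- *R0 resection, recurrence on imaging at month 10.* Synopsis: DFS is 10 months, as intended. Section 2.2: the event is clear, but the clock starts at randomization, which does not exist in a single-arm trial.
- *Gross residual tumour, first growth on imaging at month 6.* Synopsis: recurrence does not strictly describe this. If growth is taken as recurrence, DFS is 6 months for a patient who was never disease-free; if not, there is no event until death. Section 2.2: the text moves between recurrence and progression, so growth may count.
- *Residual tumour, stable at the last scan.* Synopsis: no event has occurred, so the patient is event-free. Section 2.2: censoring is at the last confirmed disease-free date, and after such an operation there is none.

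No rule in either place settles the second and third cases.

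**2. How many patients, and how far the curve could move**

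The inputs are N = 30 (synopsis) and R0 rates from Section 1. There, before the trial results, "the R0 resection rate is about 70–80" per cent in general; two earlier chemotherapy trials report 79.3% and 84% after neoadjuvant treatment. These are background figures, not planning values. A rate of 95% is added as an assumption.

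Number not R0 = 30 × (1 − r), if all 30 are operated on:

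- r = 0.70: 30 × 0.30 = 9.0
- r = 0.793: 30 × 0.207 = 6.2
- r = 0.84: 30 × 0.16 = 4.8
- r = 0.95: 30 × 0.05 = 1.5

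These are upper guides, because some patients who do not reach R0 will have no operation.

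For the curve, assume exponential times with median 36 months in R0 patients and m = 6 or 12 months to progression in the others:

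- non-R0 patients credited with time: S(t) = r·2^(−t/36) + (1 − r)·2^(−t/m)
- non-R0 patients counted as events at surgery: S(t) = r·2^(−t/36)
- gap: (1 − r)·2^(−t/m), which does not depend on the 36-month assumption

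At 12 months, 2^(−12/6) = 0.25, 2^(−12/12) = 0.50 and 2^(−12/36) = 0.794:

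| R0 rate | Credited (m = 6 to 12) | Event at surgery | Gap, points |
| --- | --- | --- | --- |
| 70% | 0.631–0.706 | 0.556 | 7.5–15 |
| 79.3% | 0.681–0.733 | 0.629 | about 5–10 |
| 84% | 0.707–0.747 | 0.667 | 4–8 |
| 95% | 0.767–0.779 | 0.754 | about 1–2.5 |

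At 24 months, 2^(−24/6) = 0.0625 and 2^(−24/12) = 0.25, so for R0 rates of 70–84% the gap is 0.16 × 0.0625 = 1 point to 0.30 × 0.25 = 7.5 points.

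An R0-only curve would stand at 0.794 at 12 months, above the credited 0.63–0.75 for R0 rates of 70–84%. The direction of the distortion depends on the comparator.

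**The case against.** The strongest reply is that this rests on silence. No sentence says that DFS is computed for every operated patient, and a statistical analysis plan, not shown here, could settle who enters the curve. That is fair as to wording: the inclusion of non-R0 patients is inferred from the absence of any restriction. But the protocol itself fixes the origin, the event and the censoring rule, in two conflicting versions, and a plan that followed either faithfully would inherit the gap.

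Second, gross residual cases should be few. The synopsis and Section 3 plan radical gastrectomy when feasible, inclusion criterion 3 requires a tumour judged suitable for R0 resection, and Section 5.1 ends the study for patients who progress and cannot have a radical resection. This stands, and it pulls the likely number down. It does not remove R1 cases, since microscopic margins are known only from pathology after surgery, and the R0 rate is itself a secondary endpoint.

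Third, a reader might infer that a patient with stable residual tumour collects long disease-free time. Section 2.2 does not support that, because its censoring rule looks for a confirmed disease-free date; the fault there is that no such date exists.

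Fourth, surgical failures are not hidden elsewhere: the R0 rate is reported over enrolled patients and overall survival runs from enrollment. That limits the harm but does not make the DFS curve interpretable.

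**Conclusion.** The point holds as a defect in the endpoint definition. Neither version of DFS requires a disease-free state after surgery, although Section 10 foresees R1 and cytoreductive operations, so the curve can mix recurrence with progression of known tumour.

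The size is uncertain. Up to about 5–6 of 30 patients would be affected if the R0 rate matched the two background trials, and 1–2 at an assumed 95%. DFS is overstated only relative to counting non-R0 patients as events at surgery: about 4–15 points at 12 months for R0 rates of 70–84%, and 1–3 points at 95%, with assumed medians of 6–12 months to progression.

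Two stronger readings are tempting but unsupported. One is that the curve is 16–21 points too high at time zero, from 1 − 0.84 and 1 − 0.793. Every Kaplan-Meier curve starts at 100%, including one restricted to R0 patients, and those rates belong to earlier trials of a different regimen. The other is that current DFS is too high in every sense; an R0-only curve would lie above it.

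DFS is a secondary, descriptive endpoint, and the primary pCR endpoint is unaffected.

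**What to change.** Write one DFS definition and use it identically in the synopsis and Section 2.2: patients with R0 resection, timed from surgery to recurrence or death from any cause. Remove the randomization origin and the restriction to deaths due to progression.

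Report beside it event-free survival from enrollment in all enrolled patients, with these events: progression that precludes surgery, non-R0 surgery (dated at surgery), recurrence, and death from any cause.

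The cost is endpoint wording and one further Kaplan-Meier curve. Margin status, imaging and survival status are already collected. Section 6.3 gives a visit schedule only for operated patients, so the new definition should also say how a patient who is never operated on and has not progressed is handled. The downside is that DFS becomes conditional on R0 resection and has fewer patients; the event-free survival curve offsets this by keeping the others in view. The wording is best settled before any DFS data are analysed.
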